## Abstract

**Introduction:**

Great improvements in the health of newborns, children, and women in Pakistan are needed. A large body of literature has demonstrated that the majority of maternal, newborn, and child deaths are preventable with essential health strategies including immunization, nutrition interventions, and child health interventions. Despite the importance of these interventions for the health of women and children, access to services continues to be a barrier. Furthermore, demand for services also contributes to low coverage of essential health interventions. Given the emerging threat of COVID-19 coupled with already weak maternal and child health, delivering effective and feasible nutrition and immunization services to communities, and increasing demand and uptake of services is a pressing and important need.

**Methods and analysis:**

This quasi-experimental study aims to improve health service delivery and increase uptake. The study included four main intervention strategies including community mobilization, mobile health teams offering MNCH and immunization services, engagement of the private sector, and testing of a comprehensive health, nutrition, growth, and immunization app, Sehat Nishani, for a period of 12 months. The target group of the project were women of reproductive age (15–49 years) and children under-five. The project was implemented in three union councils (UCs) in Pakistan including Kharotabad-1(Quetta District, Balochistan), Bhana Mari (Peshawar District, Khyber Pakhtunkhwa) and Bakhmal Ahmedzai (Lakki Marwat district, Khyber Pakhtunkhwa). Propensity score matching based on size, location, health facilities, and key health indicators of UC was conducted to identify three matched UCs. A household baseline, midline, endline and close-out assessment will be conducted for evaluating coverage of interventions as well as the knowledge, attitude, and practices of the community in the MNCH and COVID-19 context. Descriptive and inferential statistics will be used to test hypotheses. As well, a detailed cost-effectiveness analysis will be conducted to generate costing data for these interventions to effectively inform policymakers and stakeholder on feasibility of the model.

**Trial registration:**
NCT05135637.

## Introduction

The health of newborns, children, and adolescents in Pakistan is an area where progress and improvements are greatly needed [1]. Though slow gains have been made in improving maternal, newborn and child health (MNCH) indicators, the country’s under-five mortality rate still stands at 74 deaths per 1000 live births and the maternal mortality rate at 186 deaths per 100,000 livebirths [2, 3]. Alarmingly, Pakistan has the highest neonatal mortality rate globally at 42 neonatal deaths per 1000 live births [2]. A large body of literature has demonstrated that the majority of these maternal, newborn, and child deaths are preventable with essential health interventions including immunizations, nutrition interventions, and child health interventions [4]. However, access to care can be a barrier due to a poorly functioning health system limiting the provision of services [4]. Rural-urban and socioeconomic disparities and consequent health inequities also contribute to vulnerable populations experiencing worsened health indicators. Limited demand for vaccines due to sociocultural beliefs influences the demand for services, and vaccine hesitancy continues to limit vaccine uptake.

COVID-19 and related mitigation strategies to decrease its spread presented health systems globally with a daunting challenge, including the Pakistani health system. The disruption of health service delivery and reduced care seeking has increased the risk of disease and malnutrition in vulnerable populations. From April to July 2020, vaccination drives and polio supplementary immunization activities were halted, with routine vaccination rates falling owing to fear in the communities of visiting health facilities [5, 6]. As the Government of Pakistan works to strengthen the existing health systems in the context of conflict and COVID-19, it is critical that an integrated approach is taken which focuses on effective delivery platforms for providing health and immunization services where they are most required. Research models indicate that scaling up interventions in Pakistan by using appropriate delivery platforms to reach rural and vulnerable populations, via community-based strategies, could reduce maternal, newborn and child deaths by nearly 60% [7].

Given the impact of the private sector on the health system, engaging private health providers will also be an important part of any integrated strategy to improve maternal and child health [8]. In Pakistan, it is estimated that the private sector accounts for nearly three-quarters of total health services delivered [9]. Private health providers’ role in ensuring access to maternal and child health services and immunization is substantial. In these challenging contexts, private health providers can increase the availability of essential health services to high-risk communities who have limited options and poor coverage of interventions. Despite their potential importance, there has been limited research on the most effective ways to engage with the private sector.

Further to the barriers to delivering services, limited demand for services also underlies low health intervention coverage. Increasing uptake of vaccine services has proved to be a large barrier in Pakistan. Polio vaccination incites specific fears related to potential side effects, suspicions about the motives of the program, and the religious permissibility of the vaccine [10]. Addressing these concerns has been an issue for polio eradication efforts in Pakistan. Research on polio in Pakistan has demonstrated that the refusal of services is, in fact, not solely a reflection of an aversion to the service but also a lack of trust in the authorities providing services [11]. Early community engagement, particularly the engagement of elders and religious leaders can act as mechanism through which to dispel any fears or concerns related to the services provided. This is of particular importance as the literature has demonstrated exclusion from systems of power without the opportunity to ask questions can contribute to misconceptions and conspiracy theories about health services [12, 13].

Given the impact of COVID-19, coupled with already weak maternal and child health status in Pakistan, delivering effective and sustainable MNCH, nutrition and immunization services to in-need communities throughout the country is a pressing priority. Increasing efficiency through integration and increasing demand for services through improving community awareness and care seeking behaviours is also imperative to improve maternal and child health. Recognizing these challenges and opportunities, *Naunehal* aims to integrate MNCH and immunization strategies through community mobilization and private sector engagement, to create a replicable and cost-effective model that can potentially be adopted by the government for the long-term sustainability of the interventions. In the context of COVID-19, these steps have even more relevance to rebuilding primary care and immunization systems. The project also tests the use of a health, nutrition and immunization app, *Sehat Nishani* which creates an integrated interface between immunization registry, growth records and household data, to help track coverage better.

## Materials and methods

### Study objectives

Improve coverage of MNCH practices and services, particularly in the COVID-19 context including routine childhood immunization, improved breastfeeding practices, handwashing promotion, best possible sanitary practices, and optimal diarrhea management.Enhance community engagement and knowledge to improve care seeking and health behaviours.Create a replicable model of private health sector engagement that can be adopted by thegovernment for long-term sustainability of the interventions.Examine the feasibility of the intervention by assessing the cost-effectiveness of this model of delivery.Develop and pilot test a cell phone app that integrates immunization registry, birth record, child health and growth information and household data.

### Study setting

*Naunehal* was implemented in three union councils (UCs) of Pakistan, Kharotabad 1(Quetta District, Balochistan Province) and Bhana Mari (Peshawar District, Khyber Pakhtunkhwa (KP) Province) are classified as super high-risk UCs (SHRUCs) for polio, while UC Bakhmal Ahmedzai in district Lakki Marwat, KP, is an area which has experienced polio outbreaks recently (Appendix A in S1 File). In addition to high polio virus transmission, the three UCs have sub-optimal immunization coverage, maternal and under-five health, and nutrition indicators and were thus chosen for the Naunehal project.

### Study design

The project adopts a quasi-experimental prepost study design to assess the impact of the proposed interventions. The three UCs are the intervention sites and for each of these target UCs, a separate, matched control UC of comparable size, population, location and coverage indicators was identified, with propensity score matching and in consultation with local partners. The matched UC was always in the same district but never bordering the target UC. Baseline, midline endline, and close-out surveys will be conducted using the 30x7 techniques. Thirty clusters demarcated by the government’s polio program from each UC are randomly selected and 15 households with children under-five selected from each cluster. Thus, to achieve an optimal sample size, 450 households are surveyed from each of the intervention and control UCs (Table 1). The surveys focus on household characteristics, immunization coverage, health & care seeking behaviours, especially in the COVID context, and water, sanitation, and hygiene (WASH) practices.

**Table 1 pone.0287722.t001:** Sample size for household survey by UC.

Sr No.	District	Sample Size (Households)
1.	UC in Quetta	450
2.	UC in Peshawar	450
3.	UC in Lakki Marwat	450
4.	Matched control UC in Quetta	450
5.	Matched control UC in Peshawar	450
6.	Matched control UC in Lakki Marwat	450
Total		2,700

#### Intervention strategies

*Naunehal* aims to improve health service delivery and enhance uptake, by focusing on four main intervention strategies implemented in all three target UCs; community mobilization to enhance awareness and demand, mobile health teams offering MNCH and immunization services, engagement of private sector to increase immunization coverage and testing of a comprehensive health, nutrition, growth, and immunization app, *Sehat Nishani*. The target group of the project include women of reproductive age (WRA) (15–49 years) and children under-five residing in the UCs.

**Community engagement and mobilization** includes dissemination of comprehensive messaging on promotion of routine childhood immunization, optimal infant and young child feeding (IYCF) practices, handwashing, best possible sanitary practices, COVID-19 prevention, optimal diarrhea management, and appropriate care seeking for both pregnant women and young children. The messages were communicated via health promotion materials, health awareness sessions, and mosque announcements. Announcements especially encouraged the community for routine childhood immunization and to utilize *Naunehal* mobile health services and visit private practitioners’ clinics or government facilities for immunization. An integral step of the community engagement process was to map and consult with opinion leaders and influential community members, to introduce the project and gain their support for the activities.

**Mobile health services (MHS)** were deployed in each of the three pilot UCs, with *one team per UC* in the pilot phase. Each mobile team had *a female physician*, *a female vaccinator*, *and a facilitator* and visited pre-determined areas of the UC daily, for 06 days per week for 12 months. The locations kept rotating, with an effort to focus on hard-to-reach areas where access to and coverage of health facilities is limited. The team ensured that all COVID-19 -prevention recommendations of the government are followed.

The MHS provided basic health services, immunization, and health and IYCF counselling targeted towards children under-five and WRAs. The immunization services provided by the team are limited to those already approved and recommended by the Pakistan government (Appendix B in S1 File). The physician treated the young children for common childhood illnesses such as diarrhea and acute respiratory infections. Those children or WRAs requiring referral or inpatient care were referred to the nearest health facility. Consent was taken from caregivers of under-five children and participants so that details on services delivered can be shared and utilized in study analysis. Participants received services regardless of whether consent for data collection was given or not. Personal identifiers will be removed from data.

The project did not anticipate any major adverse event as routine vaccines are widely used safely. However, guidance was provided to the team physician on steps to follow in case of an adverse event, including providing emergency medication, stabilization, subsequent referral to a health facility if needed, following up on the child, and directive to return to camp after 24–48 hours for check-up. Serious and/or unexpected adverse events were to be evaluated and reported to Aga Khan University (AKU) and the SickKids Centre for Global Child Health. The information on all events was collected, assessed, and reported on Case Report Forms (CRFs) through routine reporting. If a subject suffered any injury while receiving care, he/she received free of cost, appropriate care as required and the organization would bear the cost of this care.

**Private Sector Engagement** is an innovative strategy where Naunehal aimed to create a replicable model of private sector engagement that could be adopted by the government for long-term sustainability. Private sector healthcare providers (HCPs) in the target UCs were taken on board to increase coverage of routine immunization and improve the quality of maternal and child health services. HCPs offered age-appropriate routine vaccination, including missed doses, to all under-five children visiting their clinics.

Identification of HCPs occured during the line listing of the baseline survey, and HCPs with a medical degree who were willing and whose clientele included under-five children were selected. The engaged HCPs were trained in collaboration with the District Health Office and the Expanded Programme on Immunization (EPI). Training primarily focused on immunization of neonates and young children as per the schedule and methods endorsed by EPI. Safety protocols, cold chain maintenance and vaccination recordkeeping were an integral component of the training program. As well, the HCPs were trained on use of Naunehal health promotion materials and counselling.

Project team liaised with EPI to arrange vaccines for the private practitioners and supply them on a regular, as-needed basis. The arrangement ensured that vaccines were ready to be picked up or delivered on a pre-determined day from the EPI office with cold-chain maintenance preparations to the practitioners’ clinic. These included BCG, OPV, IPV, Pentavalent, Pneumococcal, Measles and Rotavirus vaccines.

An incentive for the practitioners was to receive much promotion and exposure within the UC, during community mobilization and public announcements. As well, it was an opportunity for them to build linkages with the community and with government partners. Non-monetary incentives in the form of equipment may be offered to practitioners who administer a larger number of vaccines.

***Sehat Nishani*,** a digital health mobile application was launched in the three intervention UCs to assess the feasibility of adopting a birth, health, and immunization app to create a vaccination database and capture information on birth, birth weight, nutrition and growth records essential for follow up of the cohort. The app was developed in English and Urdu at AKU’s Technology Innovation Support Centre, specifically for Naunehal and the Urdu version was piloted during the project. Lady health workers (LHWs), lady health visitors (LHVs) in government health facilities, EPI vaccinators and partnering HCPs were engaged to use the *Sehat Nishani* app on their existing Android phones.

The health workers received the necessary orientation and training to use the app and received technical support when needed from the project team. Health workers had app access via a unique login ID and password and thus, the app was not publicly accessible. Data from a single family was linked via a unique Family ID also accessible via an assigned QR code. While LHWs and HCPs entered both vaccination and health data for under-two children and WRAs, the vaccinators only entered vaccination data. Health data for children included birth history, nutritional history, growth record, and an illness record. For WRAs, in addition to the nutritional and illness history, the app was designed to record details on antenatal care, delivery and postnatal care. Caregivers were able to log in to the app with their unique ID number and see their child’s record without making any changes or entering any information. All data in the app will be encrypted to ensure patient and household information stored is secure.

App records are stored in a cloud-based central database managed by AKU, where child health and nutrition data, vaccinator performance, vaccination rates, children overdue for vaccination, and under-immunized areas can be identified.

### Monitoring and impact evaluation

*Naunehal* has undergone rigorous monitoring and evaluation. As mentioned, household surveys are to be conducted at baseline, midline, at the end of the project to assess the impact of interventions and one year after to examine sustained effect.

The Mother & Child Care Trust (MCCT), an independent non-governmental organization based in Karachi, Pakistan, working on maternal and child health research projects, conducted an independent monitoring and evaluation of the project. MCCT has tracked the impact of the project using a range of indicators including the number of births registered, birth dose of OPV and BCG received, receipt rates of pneumococcal conjugate vaccine (PCV) and measles vaccine, immunization rates for all vaccines, and zero dose cases.

#### Household surveys

A household baseline, midline, endline and close-out assessment will be conducted for evaluating coverage of interventions as well as the knowledge, attitude, and practices of the community in the MNCH and COVID-19 context.

The inclusion criteria for a household includes consent from the family, at least one child less than 5 years of age in the household, and that the family has been living in that high-risk UC for at least 6 months (including the child in the household) prior to the day of the interview. However, the household is eligible even if the only child in household was born in the last six months. For close-out survey, the families should have been living in the UC for at least one year. Any household where a parent or caregiver is not available to answer questions related to the child’s health and immunization, will be *excluded*. Data collected will be processed and analyzed at AKU, Karachi.

A consent form outlining the objectives of the study, how privacy concerns will be handled, and how the data will be used is shared with the participants. They are given as much time as needed to review the consent form and ask any additional questions. If they feel comfortable, they can sign the form and the survey commences. If not, they are thanked for their time and not included in the survey.

The surveys will help to develop a comprehensive picture of population distribution, health intervention, care seeking and immunization coverage for children under-5 years. The baseline (Appendix C in S1 File) serves as the basis for targeting and tracking progress. Given the enormous impact that COVID-19-related mitigation strategies have had on routine health services such as antenatal care, childbirth services, immunizations and care seeking, the baseline assessment also assessed bottlenecks and helped tailor possible approaches to address these issues. The endline survey (Appendix D in S1 File) was conducted immediately after conclusion of intervention while the close-out survey will be conducted, a year after the endline to explore presence of sustained effects and persistent benefit. Implementation was conducted from 2021 to 2022, while the endline survey was conducted in 2022. The close-out survey will be conducted in 2023, while the cost-effectiveness data will also be compiled in the same year. The close-out survey, to be conducted one year after completion of intervention, will aim to assess retention, long-term benefits, and sustainability of the intervention especially with a focus on immunization coverage, IYCF practices, and care seeking behaviours.

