### Analysis

All data is captured electronically using customised applications running on android based handheld devices. Data is hosted at the Aga Khan University data center. Demographic, clinical, knowledge, attitude & practices (KAP), and MNCH related indicators data will be compiled and analyzed using STATA -version 17.0 [14].

Descriptive and inferential statistics will be used to characterize the study sample and test hypotheses. Descriptive results for all continuous variables (e.g., age) will be presented as mean ± standard deviation or median with inter-quartile range, while numbers (percentage) will be reported for all categorical variables.

To assess the independent effect of intervention, propensity score matching was employed to identify similar UCs based on geographical location of UC, population density, size of under-five population, number of health facilities and health workers, and immunization coverage. Through this process, three matched UCs are also surveyed. Among the predictors, exact matching has been enforced to achieve the balance for all predictors between the intervention and non-intervention groups.

We will calculate overall and region-specific health coverage at baseline, midline, endline and at close-out for both intervention and control group. The mean and percentage point difference in coverage between baseline and endline, and baseline and close-out will be estimated using a mixed effects linear regression model. Effect estimates will be reported with 95% confidence intervals. The clustered nature of the data will be accounted for by including each cluster as a random effect. Estimates will be adjusted for survey design and sampling weights by treating each UC as strata and clusters as primary sampling units.

Costing data for the *Naunehal* program will be collected based on a standardized template developed by J-PAL [15]. It will be explicitly mentioned what costs are being recorded including project administration, training, implementation, goods purchased, and monitoring. The costs will be measured with the consideration that *Naunehal* is a pilot project and scaling up the project may change actual costs. Base Year and Year of Analysis will be accounted for including inflation costs and exchange rates. The cost-effectiveness will be assessed on basis of number of beneficiaries reached and the program effect on key indicators, followed by determining the cost-effectiveness ratio.

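### Baseline and close-out use different residence rules (six months against one year), so the planned baseline-to-close-out change compares differently defined populations.

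*Protocol article*

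**What the plan says.** The Household surveys section gives the general inclusion rule for a household, which requires that "the family has been living in that high-risk UC for at least 6 months" before the interview. The requirement extends to the child, with one relaxation: "the household is eligible even if the only child in household was born in the last six months". A separate sentence then sets a stricter rule for the last round only: "For close-out survey, the families should have been living in the UC for at least one year". No reason is given for the change, and the text does not say whether the newborn relaxation carries over to close-out.

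On timing, the Intervention strategies section says that the mobile teams "visited pre-determined areas of the UC daily, for 06 days per week for 12 months". The Household surveys section says that the endline survey "was conducted immediately after conclusion of intervention". It describes the last round as follows: "The close-out survey, to be conducted one year after completion of intervention". That round is there to assess retention and sustained benefit.

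The Analysis section plans two changes in coverage, one from baseline to endline and one from baseline to close-out. The text on the second reads: "baseline and close-out will be estimated using a mixed effects linear regression model". The adjustments it names are a random effect for cluster, UCs as strata, clusters as primary sampling units, and sampling weights. It names no restriction or adjustment for length of residence. Coverage is to be calculated for both groups at all four rounds, but the section does not say that the changes are differenced between groups.

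**The concern.** Of the two planned changes, baseline to endline applies one eligibility rule at both ends. Baseline to close-out does not, and it is the contrast meant to show whether benefit lasts. If families resident for six to twelve months differ in coverage from longer residents, removing them from one end moves the estimate even when nothing in the community has changed.

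The named adjustments do not repair this. Sampling weights make the sample represent the eligible population, and here the eligible population itself changes. A larger sample would not remove the shift either.

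A second question is what the one-year rule achieves. A reader may take it to mean that close-out families lived through the programme, which bears on how a finding about retention can be read.

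**Working it through.** **Sample size (reproduced).** 30 clusters × 15 households = 450 per UC, and 6 × 450 = 2,700 per round. Both agree with Table 1. One arm has 3 × 450 = 1,350 households per round.

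**Presence during the programme.** Put the intervention at months 0 to 12, endline at month 12 and close-out at month 24. Latest arrival = survey month − required residence. Guaranteed overlap = 12 − latest arrival, not below 0.

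| Round and rule | Latest arrival (month) | Guaranteed overlap (months) |
|---|---|---|
| Endline, 6 months | 12 − 6 = 6 | 12 − 6 = 6 |
| Close-out, 12 months (as planned) | 24 − 12 = 12 | 12 − 12 = 0 |
| Close-out, 6 months (if the general rule were kept) | 24 − 6 = 18 | 0 |

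The one-year rule therefore removes families who arrived in months 12 to 18, all after the programme. It still admits a family that arrived just as the programme ended. Guaranteeing the same six months of overlap as at endline would take 18 months' residence (24 − 18 = 6; 12 − 6 = 6).

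**Shift within an arm.** Let s be the share of baseline-eligible households resident 6 to 12 months, and d their shortfall in coverage against longer residents, whose coverage is C. Suppose there is no real change.

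- Baseline coverage (both groups eligible) = (1 − s)·C + s·(C − d) = C − s·d
- Close-out coverage (longer residents only) = C
- Apparent change = s·d

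The apparent change is positive if recent movers have lower coverage (d > 0) and negative if they have higher coverage. Neither s nor d is in the article. Under assumed values, the size in percentage points is:

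| s | d = 5 | d = 10 | d = 20 | d = 30 |
|---|---|---|---|---|
| 2% | 0.1 | 0.2 | 0.4 | 0.6 |
| 5% | 0.25 | 0.5 | 1.0 | 1.5 |
| 10% | 0.5 | 1.0 | 2.0 | 3.0 |
| 15% | 0.75 | 1.5 | 3.0 | 4.5 |

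**Scale.** With assumed coverage of 50%, the standard error of a change in one pooled arm is √(2 × 0.5 × 0.5 / 1,350) = 1.9 points with no design effect, and √(2 × 0.5 × 0.5 / 675) = 2.7 points with an assumed design effect of 2. The 1-point and 2-point examples are thus about half a standard error and about one standard error when there is no design effect.

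**Difference of changes between arms.** The residual is s_I·d_I − s_C·d_C, with I for intervention and C for control. If the products are equal it is 0. With s = 10% against 5% and d = 20 points in both arms, it is (0.10 − 0.05) × 20 = 1.0 point. With 15% against 5% and d = 30 points, it is (0.15 − 0.05) × 30 = 3.0 points.

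**After matching the rule.** With both ends limited to one-year residents, this shift is 0. Baseline households per UC become 450 × (1 − s): 441, 428, 405 or 382 for s = 2%, 5%, 10% or 15%.

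**The case against.** The strongest reply is that the one-year rule has an evident purpose. With close-out a year after the programme, it confines the sample to families who were present by the time the programme ended, and a six-month rule would let in families who arrived later. This stands. It means that simply returning close-out to six months would gain comparability at the expense of relevance to retention. It justifies a restriction at close-out, but not leaving the baseline unrestricted in the same contrast.

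The second reply is that the design has matched controls in the same district, the rule is not limited to intervention UCs, and a shift common to both arms drops out of a between-arm comparison. This also stands, on condition that the share times the gap is equal in the two arms. Nothing in the article shows that migration differs within pairs, and nothing shows that it is equal. Changes reported within an arm stay affected either way.

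Third, a residence filter could sit in a fuller analysis plan that is not shown. That is possible. But the unequal rule is stated in the article, and the analysis described there compares across it.

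A reader might infer that the mismatch flatters the programme by making benefit look more persistent. The article does not support that: it says nothing about coverage among recent arrivals, and a between-arm residual could have either sign. A reader might also infer that families admitted at the one-year boundary had no contact with anything the project set up. That goes too far as well. The article does not say that trained private providers or changed community behaviour cease at month 12.

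**Conclusion.** The point holds as a mismatch of definitions: the two ends of the baseline-to-close-out contrast cover differently defined populations, and none of the stated adjustments restores comparability. Its size and direction cannot be determined from the article. Under assumed shares of 2% to 15% and gaps of 5 to 30 points, the shift within an arm is 0.1 to 4.5 points. It may well be small, and it is zero between arms if the share times the gap is equal in both.

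The one-year rule is useful because it excludes families who arrived after the programme. It secures presence at programme end only, so close-out results should not be described as coming from families all exposed during the programme. This is an inexpensive improvement to the plan, not a defect that undermines the study.

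**What to change.** For the close-out contrast, restrict baseline, and any other round compared with close-out, to families resident at least one year, in both arms. State how the newborn exception works and apply it identically at each round. The baseline-to-endline contrast can keep the six-month rule.

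This needs residence duration to have been recorded in the earlier rounds, which cannot be checked because the questionnaires are in appendices that are not shown. If it was not recorded, enrol at close-out under the six-month rule and record duration there. Then report the baseline-to-close-out change on the common six-month definition, alongside the close-out subgroup resident at least one year.

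The first route costs some baseline households: about 405 of 450 per UC would remain at an assumed 10% recent movers. The fallback costs one added question and one added analysis. The article describes close-out as still to come, so either route could be set before that survey.
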